The aim of this cluster randomised controlled trial is to test the effectiveness of personalised, home-based nutritional counselling of pregnant and lactating mothers by Community Health Workers (CHWs) on MIYCN practices, and consequently on morbidity and nutritional outcomes of infants in two Nairobi slums. Specifically, we aim to determine: (i) the effect of the intervention on breastfeeding and complementary feeding knowledge, attitudes and practices among mothers of infants; (ii) the effect of the intervention on nutritional outcomes among infants; (iii) the effect of the intervention on morbidity from diarrhea among infants; (iv) the experiences, and facilitating and limiting factors associated with the intervention; and (v) the cost-effectiveness of the intervention. The primary objective is to change breastfeeding practices, particularly to improve the rate of exclusive breastfeeding, which is currently extremely low in the slums [22], despite its documented importance in child survival [11]. The primary hypothesis is that personalised, home-based nutritional counselling and support of mothers in Nairobi slums by CHWs will lead to higher knowledge and self-efficacy in breastfeeding, thereby resulting in adherence to WHO guidelines for breastfeeding. This is expected to lead to improved rates of exclusive breastfeeding for six months. The CHWs will therefore counsel mothers on what they should do regarding breastfeeding and other maternal MIYCN practices and how they should do it including breast positioning and attachment and expressing breast milk, which is expected to lead to higher knowledge and self-efficacy. The proposed strategy (community-based initiative), backed by the Ministry of Health, builds on the existing MIYCN strategy by the Government and is expected to get over the problem of women having to present at hospitals to receive information. This is important for urban poor women who have limited health care access [20,21]. The backing by the Government is critical for potential scale-up of the strategy within the Kenyan health care system if it proves to be successful in the trial.

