### Clusters and study populations

Community units (CUs) in Korogocho and Viwandani that fall within the NUHDSS area will constitute the clusters to be included in the study. CUs are geographically defined units, mostly equal to a village (in our study setting) and usually have a population size of approximately 5,000 people. The CUs are defined by the Community Strategy, a Government community-based approach where CHWs provide health care services to people at the community level. The reason for choosing to work with the defined CUs is pragmatic because they are administrative areas that are defined by the health care system and any intervention moving forward in the future would need to map onto these administrative units to be effective.

Study participants will include all pregnant women aged between 12 to 49 years old, who are residents of CUs in Korogocho and Viwandani slums that fall within the NUHDSS area, and their respective children (when born). These will be recruited during pregnancy on a rolling basis until the desired sample size is achieved. The target is to recruit the women as early as possible during pregnancy, particularly during the first or second trimester. While the reproductive age in most studies is usually defined as 15 to 49 years, we include girls aged 12 to 14 years because a substantial proportion (close to 10%) of adolescents in the study areas is sexually active before the age of 15 years [28].

To be excluded from the study will be: (a) women of reproductive age who will have given birth before the proposed intervention starts; (b) women with a disability that makes delivery of the intervention difficult (for example, a hearing or sight problem, or mental handicap).

To be dropped from the analysis will be: (a) women who lose the pregnancy and/or have a still-birth; (b) women who are lost to follow-up during pregnancy; and (c) mother-child pairs of children with a disability.

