### Other data to be collected

Other data to be collected will include:

1. Baseline data; collected at recruitment before the commencement of the intervention in both the control and intervention arms. Baseline data will include:

1.a. Knowledge, attitudes and practices regarding maternal and infant feeding.

1.b. Maternal anthropometric measurements.

1.c. Household food security.

1.d. Maternal socio-demographic characteristics and socio-economic status.

2. Child motor development (self-reported by the mother using questionnaire); updated every two months during the follow-up period after delivery.

3. Dietary intake for the mother collected every two months during the follow-up period through an interviewer administered questionnaire to the mother.

4. Maternal weight, monitored every two months during pregnancy and in the first year after delivery.

5. Contextual data, including morbidity from common childhood illnesses, antenatal care, place of delivery, vaccination, household food security, water and sanitation and hygiene practices will be collected through an interviewer administered questionnaire to the mother; updated every two months (where relevant) during the follow-up period.

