### Statistical analysis

Determination of change for the primary outcome (exclusive breastfeeding) will be done at month six. Difference in duration of exclusive breastfeeding will also be determined longitudinally up to six months between the intervention and control groups. Comparison for other outcomes such as morbidity from diarrhea and malnutrition will be done longitudinally at around month three, six, nine and twelve. Analyses will involve a comparison of differences in the intervention and control groups with regard to the primary outcome (exclusive breastfeeding) and secondary outcomes (other infant feeding practices, diarrhea morbidity and nutritional outcomes), controlling for baseline measures (for example, previous breastfeeding practices) and prognostic factors (for example, Socio-economic status (SES) and household food security) if randomization of the clusters does not control for differences in these factors at baseline. Statistical methods to determine change will include analysis of covariance (ANCOVA) for continuous variables (for example, duration of exclusive breastfeeding and any breastfeeding and multinomial logistic regression analysis for categorical variables (that is, whether exclusively breastfed for six months or not) [40]. Additionally, survival analysis (proportional hazard analysis) for variables measured longitudinally (for example, duration of breastfeeding and malnutrition and multilevel modelling for repeated measures such as diarrheal morbidity will be applied. Intention-to-treat analysis [41] will be applied as appropriate. Efforts will be made to maximize follow-up of participants, using the NUHDSS framework to minimize missing information. Quantitative data analysis will mostly be done using Stata version 12.1. (StataCorp LP, College Station, Texas, USA). (See Table 2 for detailed outline of data analysis plan).

**Table 2 T2:** Data analysis outline

**Study objective**	**Outcome variables**	**Independent variable**	**Control variables**	**Type of analysis**
1. To determine the effect of the intervention on breastfeeding and complementary feeding knowledge, attitudes and practices among mothers of infants	1. Knowledge and attitude levels on breastfeeding and other infant feeding practices	Intervention status	SES^1^, food security, maternal demographic characteristics, antenatal care child morbidity	Multinomial logistic regression for rates and survival analysis for duration

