	2. Breastfeeding practices, including initiation of breastfeeding within one hour of birth, exclusive breastfeeding (for first 6 months) and duration of exclusive and any breastfeeding			
	3. Complementary feeding practices for example, optimal timing of initiation of complementary feeding and minimum dietary diversity, minimum meal frequency, and minimum acceptable diet			
2. To determine the effect of the intervention on nutritional outcomes among infants;	1. Stunting	Intervention status	SES, food security, maternal demographic characteristics, child morbidity, antenatal care, vaccination status	Multinomial logistic regression
	2. Underweight			
	3. Wasting			
3. To determine the effect of the intervention on morbidity from diarrhoea among infants	Diarrhoea morbidity	Intervention status	SES, food security, maternal demographic characteristics, child morbidity, antenatal care, vaccination status	Multilevel modeling
4. To determine the experiences, facilitating and limiting factors associated with the intervention	1. Client satisfaction	Not applicable	Not applicable	Descriptive (Outcome 1) Qualitative-thematic analysis (outcomes 2 and 3)
	2. Experiences			
	3. Limiting and enabling factors			
5. To assess the cost-effectiveness of the intervention	Cost-effectiveness	Not applicable	Not applicable	Cost-Effective Analysis

^1^SES=Socio-economic status.

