Other than just assessing the effectiveness of the interventions on breastfeeding and other infant feeding practices, this study will also determine the effectiveness of the intervention on other outcomes including morbidity from diarrhea and nutritional outcomes [48,49,52]. Studies elsewhere have indicated the effectiveness of interventions aimed at promoting breastfeeding on these outcomes. A good example of a study where these effects have been studied is the PROBIT (Promotion of Breastfeeding Intervention Trial) study in Belarus in 1996 to 1997 that involved slightly over 17,000 mother-child pairs. That study showed a significant reduction in the risk of gastrointestinal infections and a positive effect on growth of infants. The prevalence of gastro-intestinal infections was 9% in the intervention group compared to 13% in the control group (OR = 0.6; CI: 0.40-0.91; *P* <0.05). Likewise, infants in the intervention group were 106 g and 89 g heavier; and 0.50 and 0.46 cm taller at three and six months respectively compared to children in the control group (*P* <0.05) [49,52]. The effects may be related to optimal breastfeeding and other infant feeding practices on growth and morbidity.

Some limitations to this study may include bias in reporting of the primary outcome (exclusive breastfeeding). To counter this, objective breast milk analysis using the stable isotope technique will be used. It is possible that even with randomization of clusters, there will be difference in the baseline measures in the intervention and control group by chance. Analysis methods to be adopted will control for baseline differences. Additionally, given high mobility in the urban slums, some of the participants may be lost to follow-up, while some may also move to alternative group clusters. To counter this, intention to treat analysis will be adopted, while an allowance for loss to follow-up has been included in the sample size determination.

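### Table 2 adjusts the intervention effect for child morbidity and other covariates that arise after randomisation, against the protocol's own rule of adjusting for baseline differences

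*Protocol article*

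**What the plan says.** In Table 2 (Statistical analysis) the independent variable for objectives 1 to 3 is intervention status, and a separate column lists the control variables.

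- Objectives 2 (stunting, underweight, wasting) and 3 (diarrhoea): "SES, food security, maternal demographic characteristics, child morbidity, antenatal care, vaccination status". The three at issue are "child morbidity, antenatal care, vaccination status".
- Objective 1 (knowledge, attitudes and feeding practices, including exclusive breastfeeding for six months, the primary outcome): SES, then "food security, maternal demographic characteristics, antenatal care child morbidity". Vaccination is not in this row.

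The text above the table gives a narrower rule. Baseline measures and prognostic factors are to be controlled "if randomization of the clusters does not control for differences in these factors at baseline". The limitations paragraph of the Discussion likewise speaks of controlling for baseline differences.

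Other data to be collected has a baseline list: knowledge, attitudes and practices, maternal anthropometry, household food security, and maternal socio-demographic and socio-economic data. The three covariates in question are not in it. They stand in a later item, "Contextual data, including morbidity from common childhood illnesses, antenatal care, place of delivery, vaccination, household food security", which is updated every two months during follow-up where relevant.

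The Background states the aim as an effect on feeding practices "and consequently on morbidity and nutritional outcomes of infants in two Nairobi slums".

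**The concern.** A randomised comparison estimates the whole effect of the intervention as long as the model conditions only on things fixed before the intervention could act. Conditioning on a consequence of the intervention changes the question. If counselling reduces illness and less illness improves growth, a model that holds illness constant leaves out that part of the benefit. If illness and growth also share unmeasured causes, holding illness constant can make the arms unlike each other in those causes, with bias in either direction.

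At stake are the adjusted estimates for both health objectives. The economic evaluation is at stake too, because it is built on cases of diarrhoea and malnutrition averted. The covariates also sit in the row that holds the primary outcome.

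**Working it through.** **No stated figure is in dispute.** The sample size does not depend on these covariates, and it reproduces. With 2% against 12%, two-sided 5% and 80% power, the unpooled formula gives 7.849 × (0.02×0.98 + 0.12×0.88) / 0.10² = 98.3 per arm, about 196 in total. Then 196 × 3.2 = 627.2, and 627.2 / 0.80 = 784, against about 780 in the protocol.

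**Timing of each covariate**

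| Covariate | Rows of Table 2 | Can it have a value at recruitment? | Can the intervention change it? |
|---|---|---|---|
| Child morbidity | 1, 2, 3 | No, the child is not yet born | Yes, by the protocol's own aim |
| Vaccination status | 2, 3 | No | Only if more frequent visits change uptake |
| Antenatal care | 1, 2, 3 | In part | Only the part after recruitment, and only if visits change uptake |

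Recruitment is in pregnancy (Clusters and study populations), and counselling starts as soon as a woman is recruited (Intervention).

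**Role of child morbidity by objective**

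1. Objective 2: the Background and the secondary-outcome text place infant illness downstream of counselling and breastfeeding. Illness plausibly affects growth, so it is a mediator.
2. Objective 3: the outcome is diarrhoea and the covariate is an undefined child morbidity. Unless it is confined to non-diarrhoeal illness, the covariate contains the outcome.
3. Objective 1: the protocol expects exclusive breastfeeding to affect diarrhoea, so illness can be a consequence of the outcome being modelled. For breastfeeding within one hour of birth, also in this row, later illness follows the outcome and cannot confound it.

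**Size: an illustration for stunting.** The documents give no figure for the bias, so the inputs are assumptions. Let m0 and m1 be the proportion of children with morbidity in the control and intervention arms, b the rise in stunting risk with morbidity, and d the effect on stunting that does not pass through morbidity. Control stunting is set at 40%, the figure for under-fives in the Background. Clustering, interaction and shared unmeasured causes are ignored.

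- Total risk difference = d + b(m1 − m0)
- Risk difference after adjusting for morbidity = d
- Share removed = b(m1 − m0) / [d + b(m1 − m0)]

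| m0, m1 | b | d | Total | Share removed | OR, total → adjusted |
|---|---|---|---|---|---|
| 13%, 9% | 0.10 | −0.05 | −0.054 | 7% | 0.79 → 0.81 |
| 13%, 9% | 0.30 | −0.02 | −0.032 | 38% | 0.87 → 0.92 |
| 40%, 30% | 0.10 | −0.05 | −0.060 | 17% | 0.77 → 0.81 |
| 40%, 30% | 0.30 | −0.02 | −0.050 | 60% | 0.81 → 0.91 |

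The 13% and 9% are the gastrointestinal infection rates of the Belarus trial cited in the Discussion; 40% and 30% are assumed. The rows are the smallest and largest shares for b from 0.10 to 0.30 and d of −0.02 or −0.05. With b = 0 nothing is removed.

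**The case against.** **The text governs and the table is an outline.** The Statistical analysis text ties adjustment to differences at baseline, so the table might be read as a list of candidates under that rule. This stands in part: the fault is partly an inconsistency between text and table. It does not clear the table, because child morbidity and vaccination have no baseline value and the rule cannot admit them.

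**Antenatal care and vaccination are not part of the intervention.** Table 1 lists counselling on both as usual care in both arms, and some women are identified through antenatal care providers, so some of that care precedes counselling. This stands. They become consequences of the intervention only if scheduled monthly or weekly visits, against need-based visits in the control arm, change uptake. The protocol does not claim that. They are weaker cases.

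**In objective 3, child morbidity may mean other illness.** Diarrhoea has its own two-week recall, and the contextual data refer to common childhood illnesses generally. That reading is possible, but the table does not say so.

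**A stronger reading of objective 3.** A reader might infer that adjusting diarrhoea for morbidity would leave almost no effect. The documents do not support that. Suppose child morbidity means diarrhoea or other illness, the two are independent, and other illness has prevalence q0 in the control arm and q1 in the intervention arm. Among ill children the odds of diarrhoea are the marginal odds divided by q, so the conditional odds ratio is OR × (q0/q1). Only the ratio matters: if other illness is equally common in both arms, the odds ratio is unchanged, however rare that illness is. The documents give neither q0 nor q1.

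**A reading that extends the point to the analysis set.** A reader might add the exclusion "c) mother-child pairs of children with a disability" as the same fault, set against "To counter this, intention to treat analysis will be adopted". It is a separate matter. It is an analysis-set rule that applies alike to both arms, the Statistical analysis section promises intention-to-treat only as appropriate, and nothing in the documents suggests that counselling affects disability. No bias is shown from it here.

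**Conclusion.** The point holds, most firmly for child morbidity. Table 2 would condition the main estimates on a variable that arises after randomisation, that the protocol expects the intervention to change, and that may overlap the outcome of objective 3. Vaccination also arises after randomisation, and antenatal care may; for these the harm is conditional on visits changing uptake. The table is at odds with the baseline rule in the text, and the two must be reconciled.

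The expected direction is towards no effect, since benefit through reduced illness is held constant, but shared unmeasured causes could move the estimate either way. The range of none to about 60% of the stunting effect shows what is possible under the stated assumptions; it is not an estimate for this trial. No size is offered for diarrhoea or for exclusive breastfeeding. The sample size is unaffected.

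**What to change.** In the control-variable column of Table 2, for every main effect estimate, list only:

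- values recorded at recruitment: SES, baseline food security, maternal demographic characteristics, previous breastfeeding practices (the baseline measure the text itself names), and baseline knowledge and attitudes;
- the stratification factors: slum and cluster size.

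Write food security explicitly as the recruitment value, because it is also collected again during follow-up. Remove child morbidity and vaccination status from all three rows where they appear, and remove antenatal care received after recruitment. Any model that includes these should be labelled exploratory or mediation, and child morbidity should then be defined, stating whether it includes diarrhoea.

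The cost is an edit to one column and a sentence tying the table to the text. It needs no new data and no change in sample size, and should be made before the analysis.

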### Economic evaluation

An economic evaluation will be conducted to estimate the incremental cost-effectiveness of the personalised, home-based counseling compared to usual care, from the perspective of the provider. Cost-effectiveness will be determined with regards to cases of diarrhea morbidity and malnutrition averted using Cost Effective Analysis model (CEA) [42].

### Qualitative data analysis

Qualitative data will be transcribed verbatim and coded in NVIVO 10. Coding of the transcripts will be undertaken with themes being identified, for example, regarding breastfeeding and infant feeding beliefs and norms, with attention to contradiction and diversity of experiences and attitudes. Analysis will be conducted using a constant comparative method to identify themes and their repetitions and variations [43,44].

### Ethical considerations

Ethical approval has been granted by the Kenya Medical Research Institute (KEMRI), a recognized Ethical Review Committee, approved by the Government of Kenya. The investigators will uphold the fundamental principles regarding research on human subjects: respect for persons, beneficence and justice. For all data collection activities, informed consent will be sought from the eligible participants following full disclosure regarding the study before data collection is done. Proxy consent for children will be obtained from mothers.

## Discussion

This paper describes the protocol for a cluster-randomised trial whose aim is to determine the effectiveness of personalised home-based counselling of urban poor women by community health workers on breastfeeding and other infant feeding practices. Breastfeeding and optimal infant feeding promotion is an important intervention for child-survival; however, it is not yet clear which strategies are the most effective. Studies have indicated the effectiveness of counselling programs within primary health care in improving breastfeeding and other infant feeding practices particularly in high- and middle-income countries, but little evidence of this exists for low-income countries [30,45-48].

The BFHI, a WHO and UNICEF global program launched in 1991 to protect, promote, and support breastfeeding in maternity wards has been found effective in improving breastfeeding practices particularly in high- and middle-income countries [49-52]. Of concern, however, is the fact that the BFHI mainly focuses on promoting breastfeeding in the hospital setting around the time of delivery, yet in some countries, very few women deliver in health facilities [18]. Studies have found that while interventions that involve counselling/support at the health facility level are effective, there is evidence to suggest that combining hospital-based counselling/support with home-based visits is more effective. For example, in a study done in Brazil that compared two systems of delivery of breastfeeding counselling/support (a purely hospital-based system and a hospital based system coupled with home-visits), the hospital-based intervention achieved a high rate (70%) of exclusive breastfeeding during the hospital stay, but this was not sustained after discharge from hospital; at 10 days, this rate had dropped to 30%. The rate of exclusive breastfeeding from 10 days to six months was higher in the group that received home visits (45%) compared to the group with only hospital-based intervention (13%) [53]. This study will provide further input into the effectiveness of home-based counselling in an area with very limited health care access.

The timing of the counselling/support has been found to be important. Prenatal and postnatal breastfeeding counselling interventions, whether alone or in combination, have been found effective in improving breastfeeding practices including duration of exclusive breastfeeding and any breastfeeding [47,48]. In a systematic review of effectiveness of breastfeeding interventions that involved 38 trials, prenatal breastfeeding interventions significantly increased the rate of any short-term breastfeeding (1 to 3 months) rate by 39% compared to the usual care while combined prenatal and postnatal interventions significantly increased both the rates of intermediate (4 to 5 months) and long-term (6 to 8 months) any breastfeeding compared to usual care by 15% and 33%, respectively. Postnatal interventions significantly increased the rates of short-term exclusive breastfeeding (1 to 3 months) by 21%. In another systematic review that involved 20 trials, only interventions with a post-natal component were found to be effective in improving breastfeeding practices whereas there was no evidence to suggest effectiveness of antenatal counselling/support [48]. This study, which involves home-based personalised counselling/support during pregnancy and one year following delivery, will provide further evidence on the effectiveness of combined antenatal and postnatal counselling/support.

The mode of delivery of the intervention has also been found to be important. Some studies have indicated that interventions involving face-to-face contact are more effective than those not involving a face-to-face, contact such as through telephone [48]. Additionally, while interventions involving a component of lay counselling/support or structured education or professional counselling/support alone or in combination are effective in improving breastfeeding practices [30,47,54], some evidence further suggests that interventions that include a component of lay support/counselling are more effective than interventions involving structured education or professional support/counselling only [47]. Other evidence indicates that interventions involving professional support are effective in improving any breastfeeding but not exclusive breastfeeding, while lay support is effective in improving exclusive breastfeeding but has no effect on any breastfeeding [48]. This indicates that the effect of these interventions is not straightforward and more research is needed. The effectiveness of CHWs in health care delivery, particularly in child-survival programs has been indicated [46,55,56]. A study involving a non-randomised design in rural Kenya to determine the effectiveness of the Government’s Community Strategy (that involves use of CHWs to promote health in the community) found that the strategy improved the rate of exclusive breastfeeding from 20% to 52% [46], although the robustness of the methods used is questionable because it was a pre-test and post-test non-randomised, interventional study (with no control). This study will provide more insights into the effectiveness of personalised, face-face counselling/support using CHWs in promoting breastfeeding and other infant feeding practices in a setting with very limited access to professional counselling in urban slums in Kenya.

Other than just assessing the effectiveness of the interventions on breastfeeding and other infant feeding practices, this study will also determine the effectiveness of the intervention on other outcomes including morbidity from diarrhea and nutritional outcomes [48,49,52]. Studies elsewhere have indicated the effectiveness of interventions aimed at promoting breastfeeding on these outcomes. A good example of a study where these effects have been studied is the PROBIT (Promotion of Breastfeeding Intervention Trial) study in Belarus in 1996 to 1997 that involved slightly over 17,000 mother-child pairs. That study showed a significant reduction in the risk of gastrointestinal infections and a positive effect on growth of infants. The prevalence of gastro-intestinal infections was 9% in the intervention group compared to 13% in the control group (OR = 0.6; CI: 0.40-0.91; *P* <0.05). Likewise, infants in the intervention group were 106 g and 89 g heavier; and 0.50 and 0.46 cm taller at three and six months respectively compared to children in the control group (*P* <0.05) [49,52]. The effects may be related to optimal breastfeeding and other infant feeding practices on growth and morbidity.

Some limitations to this study may include bias in reporting of the primary outcome (exclusive breastfeeding). To counter this, objective breast milk analysis using the stable isotope technique will be used. It is possible that even with randomization of clusters, there will be difference in the baseline measures in the intervention and control group by chance. Analysis methods to be adopted will control for baseline differences. Additionally, given high mobility in the urban slums, some of the participants may be lost to follow-up, while some may also move to alternative group clusters. To counter this, intention to treat analysis will be adopted, while an allowance for loss to follow-up has been included in the sample size determination.

